### Outcomes

The main outcome of this study is to compare the time required in minutes for the cardiovascular parameters to return to their initial values between the two techniques: ICA with the QuickSleeper™ system versus the reference technique: inferior alveolar nerve block (IANB). The timing of the evolution of the parameters is based on 3 phases: “baseline” from T0 to T+4 minutes, “anaesthesia” from T+4 to T+8 minutes, and “pulpotomy” from T+8 to T+14 minutes. The return to baseline values will be defined as a success if 3 successive values of heart rate and blood pressure (systolic and diastolic) are identical to those recorded before injection. On the other hand, if there is an absence of 3 successive values of these two parameters, it is defined as a failure.

Secondary outcomes include:The O^2^ measurement performed during the 3 phasesThe efficacy of the anaesthesia with a VAS (visual analogue scale) of 0 and that the pulpotomy was completed successfully: the patient is asked about his or her perception of pain before the operation at D0 and D+1, D+2, and D+3Post-operative careInvestigation of factors associated with delay in recovery of cardiovascular parameters (heart rate, dental anxiety, age, gender, and use of analgesics in the 6 h before surgery)

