### Determination of sample size

The sample size calculation was based on the noninferiority hypothesis in a pilot study that there will be an expected mean difference of 1 min 30 s between the two anaesthetic techniques with regard to the time taken for the values to return to the initial ones. According to the reported results from the few studies available, the proportion of patients having successful anaesthesia and better pain control in the reference group (intraosseous anaesthesia) would be 93%. The noninferiority margin was defined as 20%. The significance was set at 1.7% for the 3 main criteria (heart rate, systolic and diastolic blood pressure) and 5% for the secondary criteria. Thus, using a bilateral test with an epiR package 0.98-87 (Biostatgv), 72 patients (36 patients per arm) will be included in the study.

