### Statistical analysis

The analysis will be based on intention-to-treat (ITT) using the “missing=failure” strategy. A robustness analysis, supported by the per-protocol approach, will be carried out if the patients present with protocol deviations (error of randomisation). Qualitative variables will be described by the percentages and numbers of each modality. Quantitative variables will be described by means and standard deviations. Confidence intervals at 95% will be presented.

A paper case report form (CRF) will be created for each patient inclusion for data collection and will be based on the establishment of a clinical database. All information required by the protocol must be provided in the CRF, necessary for statistical analyses.

To assess the primary endpoint (time to return to baseline heart rate and blood pressure), the mean values will be estimated by the Kaplan-Meier method (survival curves) and compared using Log-Rank tests. To assess the secondary endpoint (time to baseline O_2_ and change in measurements over time), the 2 arms will be compared in the same way as the heart rate and blood pressure parameters. Univariate and multivariate Cox models will be used to investigate the factors associated with the time to the baseline of cardiopulmonary constants. The difference in pain between D0 and D+3 will be compared between the 2 groups a Student’s *t*-test or a Wilcoxon test. Data for the analysis are collected from the first questionnaire (French version of Corah’s dental anxiety scale), the three phases of cardiopulmonary monitoring, the VAS assessment, and the postoperative questionnaire given to the patient at the end of the procedure. The information recorded on the postoperative questionnaire will be collected by a telephone call 3 days after the procedure. All the data collected will be typed and inserted into an Excel spreadsheet for data entry in a secure computer network of Nantes University Hospital. The investigative team, mainly the investigators as well as the study technicians involved in this study protocol will have access to the data collected.

In regard to the post-trial care, the patients will either continue their dental care with their appointed dentist, or in the case where they do not have one, they will be following appointments at the Nantes University Hospital.

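### Primary endpoint: return to baseline requires exact equality with an undefined reference value, a rule that truly recovered patients can hardly meet when the three parameters are scored jointly and seldom meet one by one at 1 to 2 min readings

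*Protocol article*

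**What the plan says.** Under Outcomes, the primary outcome is the time in minutes for the cardiovascular parameters to return to their initial values. Success requires that "3 successive values of heart rate and blood pressure (systolic and diastolic) are identical to those recorded before injection", and "if there is an absence of 3 successive values of these two parameters, it is defined as a failure". Baseline is a phase from T0 to T+4 min. Anaesthesia follows to T+8 and pulpotomy to T+14, so follow-up after baseline lasts at most 14 − 4 = 10 min.

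Under Statistical analysis, for this endpoint "the mean values will be estimated by the Kaplan-Meier method (survival curves) and compared using Log-Rank tests", within an intention-to-treat analysis that counts missing as failure.

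Under Determination of sample size, "The significance was set at 1.7% for the 3 main criteria (heart rate, systolic and diastolic blood pressure"), which treats the parameters as three separate endpoints. Outcomes, by contrast, puts them in one rule. No tolerance, band or rounding convention appears anywhere in the article.

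**The concern.** Physiological readings scatter around a patient's level even when nothing is happening. A rule of three consecutive exact matches therefore tests how still the readings are, not whether the patient has recovered. The reference is also unclear: a 4-minute phase can hold several differing values, and the text does not say which of them counts. Patients arrive in acute pain, and the Discussion names fear and anxiety as main causes of a raised heart rate. Someone who calms to below the starting value without an earlier qualifying run is scored as never having returned.

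The trial was set up to examine a transient heart-rate rise after intraosseous injection. If the event is rarely attainable in either arm, both survival curves stay near their starting level and the comparison says little about that rise. If a tolerance is improvised once results are known, the primary endpoint has been chosen after seeing the data.

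**Working it through.** **The plan's own figure.** The article gives no expected frequency for this event. Its 72 patients rest on 93% anaesthetic success and a 20% margin, with no power stated. With n per arm = (z₁₋α + z₁₋β)² × 2p(1−p)/δ² and p = 0.93, δ = 0.20, the last factor is 2 × 0.93 × 0.07/0.04 = 3.255. At 1.7% two-sided (z = 2.387), 36 per arm gives √(36/3.255) − 2.387 = 0.939, or 82.6% power. That calculation concerns a different outcome, so it never tests whether return to baseline is attainable.

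**Assumptions.** The article gives no within-patient SD or reading interval. The ranges tried for heart rate/systolic/diastolic SD were 2/3/2, 3/5/4 and 5/8/6 (bpm, mmHg, mmHg). The correlation between readings 1 min apart was 0, 0.5 or 0.8, and readings came every 10 s, 30 s, 1 min or 2 min. There is no drug effect, so every simulated patient is at baseline throughout.

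**Hand check.** Take SD 3/5/4, independent integer readings every minute, and a reference at the patient's true level. The chance that one reading matches is about 1/(SD × √(2π)): 0.133, 0.080 and 0.100. Ten readings contain 8 possible runs of three, so the chance of success is at most about:

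- heart rate: 8 × 0.133³ ≈ 1.9%
- systolic: 8 × 0.080³ ≈ 0.4%
- diastolic: 8 × 0.100³ ≈ 0.8%
- all three at the same readings: 8 × (0.133 × 0.080 × 0.100)³ ≈ 1 in 100 million

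**Simulation.** Readings were integer-rounded and first-order autoregressive, and success was any run of three exact matches. At the same SDs with correlation 0.5, 1-min readings and the last pre-injection reading as reference, success was 1.4%, 0.3% and 0.6%, and jointly 0 of 200,000. Over the whole range, with the last reading or the rounded baseline mean as reference:

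| Reading every | Joint rule | One parameter alone |
|---|---|---|
| 1 to 2 min | 0 to about 0.02% | about 0.01 to 10% |
| 30 s | 0 to about 0.02% | about 0.1 to 30% |
| 10 s | up to about 1% | heart rate 1 to 77%, systolic 0.3 to 55%, diastolic 0.8 to 79% |

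The smallest joint figures rest on a handful of simulated successes. At 10 s, heart rate reaches about 30 to 80% only with SD 2 to 3 and correlation 0.5 to 0.8. With SD 5 it is 1 to 24%.

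**Effect on the log-rank test.** Power = Φ(ln(HR) × √(d/4) − 2.387) for d events at 1.7% two-sided, with a hazard ratio (HR) of 2:

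- d = 2: 0.693 × 0.707 − 2.387 = −1.897, power 3%
- d = 7 (10% of 72): 0.693 × 1.323 − 2.387 = −1.470, power 7%
- d = 22 (30% of 72): power 22%
- d = 72 (every patient returns): power 71%

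**Would a loose band do?** The Background cites heart-rate rises of 9 to 10 bpm for one intraosseous system and 8 to 28 bpm for another. A 10% band is about 8 bpm at an assumed rate of 80. With SD 3, correlation 0.5, 10 readings and the baseline mean as reference, a heart rate held 9 bpm above baseline for the whole window is scored as returned in about half of cases. Such a band would hide the effect under study.

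**The case against.** The strongest reply is that the joint result depends on one reading of the text. The 1.7% level for three criteria, and the plural log-rank tests, point to scoring each parameter separately. A monitor running throughout the intervention may also record often. On that reading heart rate, the parameter of most interest, could meet the rule in a majority of patients. This stands: a reader might infer that nearly every patient in both arms must be scored a failure, and the article does not support that for heart rate read every 10 s. It remains likely for readings 1 to 2 min apart, whichever parameter is scored.

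A second reply is that the rule may mean falling within the range of the baseline-phase values. With 1-min readings and SD 3/5/4, success is then about 52 to 75% per parameter. But the text asks for equality and does not mention a range. That the two readings give such different answers is a reason to correct the wording.

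A third reply is that the full protocol may give the reading interval and the derivation of baseline. That is fair, and their absence from an article is not the complaint. The complaint is the equality rule that the article does state.

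A reader might also infer that the trial will declare the techniques similar whatever the truth. The Discussion does hope for that conclusion, but reaching it would require treating a non-significant log-rank test as non-inferiority, which is a separate question.

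**Conclusion.** The concern holds in qualified form. Scored jointly, as Outcomes is worded, essentially no truly recovered patient meets the event definition; this was stable over every SD, correlation and interval tried. Scored per parameter, about 90% or more still fail at 1 to 2 min readings, while the result for frequently read heart rate is open. Where events are that rare, the primary comparison has about 3 to 7% power even against a doubled hazard and cannot show slower recovery after intraosseous anaesthesia. The percentages rest on assumed variability and reading interval. The missing tolerance and the undefined reference value rest on the text alone. Because this is the primary endpoint, the definition needs correcting before analysis.

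**What to change.** - Take the reference for each parameter as the mean of its T0 to T+4 readings.
- Define return as the first of three consecutive readings inside a pre-specified band around that reference.
- Set each band from baseline-phase within-patient variability, without reference to arm. The heart-rate band must be narrow enough that a sustained rise of the size cited in the Background (8 to 10 bpm or more) is not scored as returned; a 10% band fails this.
- State the reading interval, whether scoring is per parameter (consistent with the 1.7% level) or joint, and how values that settle below the reference count, for all three parameters.
- Censor patients without return at T+14.
- Derive the event by program from the recorded readings.

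Settle all of this before any comparison by arm. Only patients are blinded, so a promise to act before unblinding gives little protection.

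The cost is one definition applied to readings already recorded, with no new data. The bands must be justified, and the change may be late: Trial status puts the start of recruitment in March 2019 and the last inclusion at 1 July 2022. If made after recruitment, it should be reported as a change to the primary endpoint definition.

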Intra-osseous computerised anaesthesia (ICA), such as the QuickSleeper™ system (Dental Hi-Tec, Cholet, France), administers the solution with a computerised control into the diploë (a richly vascularized bone) at a local rate and pressure. Thus, the QuickSleeper™ system is a form of ID in which the anaesthetic is delivered close to the root apices and associated periradicular tissues, leading to a greater reduction in periradicular sensation. The anaesthesia takes effect more rapidly since the solution is deposited close to the apex of the tooth at an axis of 15° to 30°. Thus, this form of delivery increases its effectiveness and reduces the risk of tissue necrosis, with better pain control (42 to 93% according to studies) [22, 23]. No soft tissue numbness occurs, and relatively fewer amounts of anaesthetic solution are needed. However, due to the fast diffusion of the anaesthetic solution in the diploe, the heart rate accelerates via the added effect of vasoconstrictors. This elevation is transient, and its effect is negligible and does not pose serious cardiovascular risk [12, 22].

There are currently many clinical studies that have evaluated cardiac parameters during IO administration. The heart rate increases in a reversible manner depending on the speed of injection [12]. The Stabident™ system showed a significant increase in heart rate of 8-28 beats/minute (BPM) on average with 2% lidocaine 1:100,000 epinephrine according to 3 authors [24–26]. By comparison, the X-Tip injection elevated the heart rate by 9–10 beats per min [27]. In regard to other parameters such as oxygen saturation and blood pressure, Pereira et al found no differences in either of them when using the X-Tip™ system but noted a significant increase in heart rate with 4% articaine (1:100,000 or 1:200,000 epinephrine) for anaesthetizing irreversible pulpitis lower molars [23]. Therefore, the accelerated heart rate could be a potential adverse effect of this injection [27].

Articaine is a common anaesthetic agent and a member of the amide family. The presence of its thiophene group increases its liposolubility, facilitating its diffusion into both nerve sheaths (such as the inferior alveolar nerve) and neural membranes of individual axons comprising a nerve trunk. The lower pKa of articaine would translate into a greater percentage of the drug in the active base form and its plasma protein binding is 95% higher than most other local anaesthetics [25–27].

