### Interventions

The patient will be blinded to the affected group and will fill out the first questionnaire which is the French version of Corah’s dental anxiety scale [31] to assess his or her anxiety about dental care. Then, the patient will be placed with a cuff on the arm, and a pulse oximeter on the other finger connected to a blood pressure monitor to monitor the cardiovascular parameters (heart rate, systolic and diastolic blood pressure, and oxygen saturation) throughout the intervention.

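### Return to baseline needs three readings 'identical' to the pre-injection ones, with no tolerance or reference value, so most recovered patients would be scored as failures if the rule is applied literally

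*Protocol article*

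**What the plan says.** The Outcomes section of the protocol article defines the primary event. Return to baseline is a success if "3 successive values of heart rate and blood pressure (systolic and diastolic) are identical to those recorded before injection". Otherwise, "if there is an absence of 3 successive values of these two parameters, it is defined as a failure". The baseline phase runs from T0 to T+4 minutes, and the anaesthesia and pulpotomy phases take observation to T+14, so at most 10 minutes follow baseline.

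The Interventions section describes the measurement: "a cuff on the arm, and a pulse oximeter on the other finger connected to a blood pressure monitor", used "to monitor the cardiovascular parameters (heart rate, systolic and diastolic blood pressure, and oxygen saturation) throughout the intervention". No reading interval is given.

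Under Statistical analysis, for time to return, "the mean values will be estimated by the Kaplan-Meier method (survival curves) and compared using Log-Rank tests". Cox models are added for associated factors. Missing data are covered by this sentence: "The analysis will be based on intention-to-treat (ITT) using the “missing=failure” strategy". Determination of sample size sets 1.7% significance for each of three main criteria: heart rate, systolic pressure and diastolic pressure.

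No section adds a tolerance, a rounding rule, or a statement of which baseline reading (last, mean or range) is the reference.

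**The concern.** Heart rate and cuff pressure are recorded in whole units and vary by a few units between readings, even when a person's true level is constant. A rule of exact equality, three times running, therefore tests mainly whether noise happens to repeat. The reference is also undefined, because several readings are taken over four minutes and will differ among themselves.

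This is not a detail that an article leaves to a fuller plan. The article states the event rule, and the rule as stated misclassifies recovered patients.

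The primary analysis depends on events. If few recovered patients can have one, the Kaplan-Meier curves stay high in both arms and the log-rank test and Cox models lose their information. Scoring missing data as failure can only lower the count further. Sampling speed matters too. A pulse oximeter can report far more often than a cuff can inflate, so three successive values is a different test for heart rate than for pressure.

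**Working it through.** **No planned figure to reproduce.** The article gives no expected proportion returning to baseline. The 93% and the 20% margin under Determination of sample size concern successful anaesthesia.

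**Inputs.** From the article: exact equality on three successive readings, and a window from T+4 to T+14. Assumed, because the article is silent: within-patient SD, number of readings, autocorrelation (0 or 0.5 unless stated), and reference (last baseline reading, or rounded mean of the baseline readings). All simulated patients are fully recovered, with a true level equal to baseline.

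**Hand check, heart rate.** For whole-number readings around a reference equal to the true level, the chance of an exact match is about 1/(SD × √(2π)). Ten readings contain 8 windows of three, so with independent readings the chance of at least one run is at most 8 × p³.

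- SD 2: p = 0.199, and 8 × 0.199³ = 6.3%
- SD 3: p = 0.133, and 8 × 0.133³ = 1.9%
- SD 4: p = 0.100, and 8 × 0.100³ = 0.8%

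These are upper bounds, because windows overlap and the reference is itself noisy. For all three parameters at SDs 2/3/2 (heart rate/systolic/diastolic), p = 0.199 × 0.133 × 0.199 = 0.0053, and 8 × 0.0053³ is about 1 in a million.

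**Simulation, recovered patients with at least one qualifying run.**

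| Assumption | Heart rate | Systolic | Diastolic | All three |
|---|---|---|---|---|
| 10 readings, SD 2-4 / 3-6 / 2-4 | 0.4-5% | 0.1-2% | 0.4-5% | at most 1 in 200,000 |
| 10 readings, SD 1 / 2 / 1 | 15-24% | 3-5% | 15-26% | under 0.02% |
| 40 readings (every 15 s), SD 2-4 | 2-23% | – | – | – |
| 120 readings (every 5 s), SD 2-4, autocorrelation 0.5-0.9 | 8-86% | – | – | – |

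Of 72 recovered patients, the first row gives 72 × 0.004 = 0.3 to 72 × 0.05 = 3.6 heart-rate events, and 72 × 0.001 = 0.1 to 72 × 0.02 = 1.4 systolic events.

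**What few events cost.** Log-rank power for an illustrative hazard ratio of 2 at two-sided 1.7% is Φ(√(d/4) × ln 2 − 2.387), where d is the number of events.

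- d = 5: Φ(0.775 − 2.387) = 5%
- d = 10: Φ(1.096 − 2.387) = 10%
- d = 72: Φ(2.941 − 2.387) = 71%

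**Would a simple percentage band do?** A band of ±10% looks natural. At 75 bpm it is 7.5 bpm, just under the smallest rise in the Background section's "significant increase in heart rate of 8-28 beats/minute (BPM) on average". At 85 bpm it is 8.5 bpm, which is above it. I simulated patients who stay 8 bpm above baseline for all ten readings (SD 2-4 bpm):

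- ±10% scores 38-55% of them as returned at 75 bpm, and 57-69% at 85 bpm.
- ±15% scores 85-100% as returned.

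Such a band accepts recovered patients but does not reject patients who have not recovered.

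**The case against.** A reader might infer that the primary comparison is bound to be almost without events, and that the trial cannot answer its question. The documents do not support that flat statement, for four reasons.

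- **Cadence and noise are unknown.** With an SD near 1, or with heart rate read every few seconds, heart-rate events can be common. This stands. But those events are matches by chance whose frequency follows the sampling rate, so the rule still does not measure recovery. Fast sampling also does not help cuff pressures.
- **The wording is plural.** The rule could mean within the range of the baseline-phase readings. With ten readings and SDs of 1-6 units, about 60-88% of recovered patients then qualify per parameter. Across 5 to 20 readings the joint figure is 3-66%. The text does not say this, so it is a possible intention and not the stated rule.
- **Joint or separate.** The Outcomes sentence reads as joint, but the split of significance over three criteria points to separate tests. The per-parameter figures should therefore lead, and the near-zero joint figure should not carry the argument.
- **The pilot.** The expected difference of 1 min 30 s suggests that return times could be observed, so a working tolerance may exist. If so, it is not in the article, and it needs to be written down because its width would drive the result.

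**Conclusion.** The point holds in this form. The stated event rule has no tolerance and no defined reference, and on its literal reading most truly recovered patients are counted as failures. With SDs of 2-4 bpm, 3-6 mmHg and 2-4 mmHg and ten one-minute readings, at most about 5% qualify on any single parameter and essentially none on all three.

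The size rests on assumed noise, interval and autocorrelation. The direction is firm for cuff pressures read about once a minute, although diastolic pressure at an SD of 1 reaches 15-26%. For heart rate the event count could be low or high depending on cadence, and in neither case does it reflect recovery. Because this rule feeds the log-rank and Cox analyses directly, it should be corrected before the arms are compared.

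**What to change.** Replace 'identical' in the Outcomes section with the following.

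1. **Reference:** each patient's mean of the T0 to T+4 readings for that parameter.
2. **Event:** defined separately for heart rate, systolic and diastolic pressure, as the first of three successive readings within a pre-specified tolerance of that mean.
3. **Interval:** one stated reading interval for each parameter, the same in both arms.
4. **Tolerance:** set before unblinding, from the within-patient variability of the baseline-phase readings pooled over arms. Check by simulation that it accepts patients who are back at baseline and rejects a sustained rise of the size the trial seeks to detect. The sponsor must state that size. The 8 bpm in the Background section comes from a different intraosseous system.
5. **Sensitivity:** report a narrower and a wider tolerance, and use the same definition in the log-rank and Cox analyses.

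Do not adopt ±10% or ±15% merely because 10% of a typical heart rate falls below 8 bpm. Adding a ±15% sensitivity analysis would not expose the problem, since it passes still more unrecovered patients.

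The cost is a few sentences and reprogramming of the derived variable from the readings already recorded, at an interval those records support. The tolerance remains a judgement and its width matters. At SDs of 3/5/4 and 5-10 readings, ±5 units accepts 51-99% of recovered patients per parameter and ±10 units accepts 93-100%.
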